### Study Population and Participant Recruitment

The study population is sourced from 3 MSM-friendly CBOs located in different regions. The inclusion criteria for community organizations are: (1) the organization must meet the sample size requirements for the project; (2) there must be a willingness to collaborate, making PrEP promotion a work priority; and (3) the organization should have a good partnership with local hospitals or centers for disease control and prevention to coordinate with disease control specialists and HIV specialists. Community collaborators participate in project training, assist with participant recruitment, support baseline and follow-up surveys, and help with quality control. Participants included in this study must meet the following criteria: (1) aged 18 years or older; (2) assigned male sex at birth and have had sexual intercourse with men in the past 6 months; (3) HIV negative at the start of the study; (4) no prior PrEP using experience; (5) willing to participate in the PrEP intervention and voluntarily consent to complete data collection and follow-up according to the assigned protocol; (6) classified as high risk for HIV infection in the past 6 months as suggested by the “Expert Consensus on HIV Pre-Exposure Prophylaxis in China (2023)” [7]. Participants are excluded if they meet any of the following criteria: (1) HIV positive, or unaware of their HIV status and refuse to undergo HIV testing; (2) have a health condition that makes PrEP unsuitable; and (3) have cognitive impairments or other severe illnesses that may affect the informed consent process.

The sample size calculation was based on the formula for an individually randomized controlled trial, assuming a 2-sided significance level (*α*) of .05 and type II error rate (*β*) of .10 (90% power). Based on extant literature and a 2021 multicenter PrEP survey in China indicating a median current PrEP usage rate (*p₁*) of 5% among MSM, the target post-intervention usage rate (*p₂*) was set at 20%. This yielded a minimum requirement of 100 participants per group. Accounting for an anticipated 15% attrition rate, the sample size was increased to 126 participants per group, resulting in a total target enrollment of 378 participants (126 per group) across 3 CBOs.

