#### Evaluation of Intervention Effectiveness

This study will use mixed-effects models to evaluate the effectiveness of primary and secondary outcome indicators. Different evaluation models will be selected based on the type of outcome indicators. Individual participants will be the unit of analysis. For the evaluation of categorical variable effects, a generalized mixed linear model will be used, reporting the adjusted odds ratio. For continuous variable effects, a mixed linear model will be used, reporting the adjusted mean differences between groups. The effectiveness evaluation will adhere to the intention-to-treat principle, including all randomized participants in the analysis. Stratified analysis will be conducted based on participants’ age, education level, income level, sample source, and city characteristics to explore evidence of effects related to these various characteristics. Statistical analyses will be performed using R (R Foundation for Statistical Computing) and SPSS software (IBM Corp), with a *P* value<.05 considered statistically significant. The study assumes that missing values are randomly distributed, and missing data will be handled using maximum likelihood estimation. Sensitivity analyses will be conducted after imputing missing values using multiple imputation methods.

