## Results

The trial is a 3-arm, parallel-group, randomized controlled trial conducted in collaboration with 3 CBOs located in Mianyang (Sichuan Province), Zibo (Shandong Province), and Hohhot (Inner Mongolia), China. The study protocol was funded in December 2025. Key operational phases, from recruitment to analysis, with specific dates and participant flow, are presented in Figure 1.

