### Participant Recruitment

Participant recruitment and screening were conducted from October to December 2025. During this period, 743 eligible MSM from the 3 CBOs were initially identified and assessed. Of these, 362 individuals were excluded for the following reasons: failure to meet predefined inclusion criteria (n=306), declining to participate (n=52), or other logistical reasons (n=4). Consequently, 381 participants provided written informed consent and were formally enrolled in the study. These 381 participants were randomly allocated into 1 of 3 study arms using a computer-generated sequence: HAPA-based cognitive behavioral intervention group (n=128), HAPA plus GCEI intervention group (n=126), and control group (n=127).

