Several practical and operational considerations are crucial to ensuring the trial’s success. To maintain participant engagement and facilitate follow-up, providing clear and accessible information about the study and PrEP is essential. Regular reminders through various communication channels will be used to enhance retention rates. Furthermore, standard training for all staff involved in participant recruitment and data collection will be implemented to ensure high-quality and consistent data throughout the study.

However, this study does have potential limitations. First, the generalizability of the findings may be affected by the implementation through selected CBOs in specific urban Chinese settings, which may limit applicability across different cultural and socioeconomic contexts. The 3-month intervention period may not capture long-term behavioral patterns, suggesting that future studies should incorporate extended follow-up assessments. Additionally, the effectiveness of economic incentives could be influenced by external macroeconomic factors and individual attitudes toward financial rewards, though socioeconomic status will be included as a moderating variable in the analysis.

This study demonstrates several key strengths. An innovative intervention model has been designed by integrating eHealth technologies with established CBO partnerships. The WeChat-based platform is implemented in collaboration with 3 well-established MSM-friendly CBOs (each with 5‐10 y of documented HIV prevention experience), creating a potentially replicable implementation framework. The study design includes comprehensive pilot testing of behavioral change techniques prior to full implementation, with systematic application of HAPA theory across all intervention components. Both individual-level and group-level mechanisms have been carefully operationalized to allow for thorough evaluation. The hybrid intervention approach (combining digital and in-person components) addresses several implementation challenges. Existing social networks will be leveraged through CBO infrastructures, while privacy concerns will be mitigated through discreet eHealth communication channels. The protocol includes specific strategies for cost-effective scaling in resource-limited settings. These design features may provide valuable insights for bridging the intention-behavior gap in PrEP uptake among key populations.

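### The exploratory subgroup plan names stratified analyses but no arm-by-factor interaction test, so it does not test whether the effect differs, and the Discussion's moderator statement does not match it

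*Protocol article*

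**What the plan says.** The section Evaluation of Intervention Effectiveness plans a stratified analysis by age, "education level, income level, sample source, and city characteristics to explore evidence of effects related to these various characteristics". The following sentence names the software and sets P<.05 as the significance threshold for statistical analyses in general, with no separate rule for subgroups. The main model is a generalized mixed model reporting adjusted odds ratios, by intention to treat. No arm-by-factor interaction term is mentioned.

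The Discussion, on limitations, adds: "though socioeconomic status will be included as a moderating variable in the analysis". In usual language a moderator is assessed by its interaction with treatment. Education and income, the natural measures of socioeconomic status, appear in the analysis section only as stratification factors.

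On sites, the Results describe a trial "conducted in collaboration with 3 CBOs located in Mianyang", Zibo and Hohhot: three organizations in three cities.

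**The concern.** Estimating the effect within each stratum answers whether there is an effect in that stratum. The stated purpose, to explore effects related to these characteristics, needs a different contrast: whether the effect differs between strata. Under a general P<.05 rule, the easy misreading of stratified results is that the intervention works in one city and not in another because one P value falls below .05 and another does not. With strata this small, that pattern is likely even when the effect is the same everywhere.

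Two further features add to this. With three cities, any characteristic of a city is fully determined by which city it is, so city characteristics cannot be separated from city or CBO. And at the planned control rate several strata may well have no control events, in which case the maximum-likelihood odds ratio is infinite or undefined.

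At stake are the subgroup statements in the final report, not the primary comparison.

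**Working it through.** **Inputs**
- Planning rates 5% and 20%, two-sided alpha .05, power 90%: Study Population and Participant Recruitment.
- Controls per city: Mianyang 41, Zibo 42, Hohhot 44 (Table 1). About 42 per arm per city is used below.
- Smallest control strata in Table 1: junior high school or below 9, master's or above 11, income above CNY 9000 15.

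**The plan's own figure.** The article states: "This yielded a minimum requirement of 100 participants per group". With the pooled formula, n = [1.96·√(2·0.125·0.875) + 1.2816·√(0.05·0.95 + 0.20·0.80)]² / 0.15² = (0.917 + 0.584)² / 0.0225, just over 100, rounded up to 101. The stated 100 is reproduced within rounding. It powers one whole-arm comparison, not a comparison within a city.

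**Expected control events per city at 5%**
- Mianyang 41 × 0.05 = 2.05; Zibo 42 × 0.05 = 2.10; Hohhot 44 × 0.05 = 2.20.
- Chance of no event, 0.95ⁿ: 12.2%, 11.6% and 10.5%.

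**Small strata, chance of no control event at 5%**
- n = 9: 0.95⁹ = 63%.
- n = 11: 0.95¹¹ = 57%.
- n = 15: 0.95¹⁵ = 46%.

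**Power within one city if the true effect is 5% versus 20% everywhere.** Exact binomial enumeration, 42 versus 42, gives 44.3% for Fisher's test and 59.5% for Pearson's.

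**Chance that the three cities disagree at P<.05** (one intervention-control contrast, cities independent, common power p): 1 − p³ − (1 − p)³.
- Fisher: 1 − 0.087 − 0.173 = 74%.
- Pearson: 1 − 0.211 − 0.066 = 72%.

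**Sensitivity to the rates.** At an assumed 15% versus 45%, exact per-city power is 82% (Fisher) to 87% (Pearson).
- Fisher: 1 − 0.550 − 0.006 = 44%.
- Pearson: 1 − 0.664 − 0.002 = 33%.

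At assumed control rates of 10-15%, a city would have about 4 to 7 control events instead of 2.

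**What an interaction test could detect** (Wald variance of a log odds ratio, 42 per arm per city)
- An arm at 5% contributes 1/(42·0.05·0.95) = 0.501; an arm at 20% contributes 1/(42·0.20·0.80) = 0.149.
- City A, 5% versus 20% (odds ratio 4.75): variance 0.650. City B, 5% versus 5% (odds ratio 1): variance 1.003.
- Standard error of the difference: √1.653 = 1.286. Log 4.75 = 1.558. Power = Φ(1.558/1.286 − 1.96) = 23%.

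**The case against.** The strongest case against runs as follows.

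- **The text says explore.** A reader might infer that the trial will declare subgroup effects from within-stratum P values. The article does not say so. The P<.05 sentence is general, and the stated hypotheses concern arms only. This stands: the article calls the analysis exploratory and makes no confirmatory subgroup claim.
- **Moderation is already promised.** Stratum estimates beside a moderation test are ordinary practice, not contradictory methods. This stands in part: the two can coexist, but the analysis section names only one of them, and the Discussion covers socioeconomic status alone.
- **The detail may sit in an SAP that is not shown.** Coding, display and multiplicity rules for exploratory analyses are fairly left there. The point here is narrower: the method that the article does name does not serve the purpose it gives, and it does not match the article's own Discussion.
- **Sample source may not be the CBO.** A reader might infer that it duplicates city. With three CBOs in three cities that is likely, but the term is not defined and could mean a recruitment channel.
- **The sizes depend on 5%.** That figure comes from a survey of current use, not of initiation among consenting high-risk volunteers, and the Introduction cites 65-89% initiation with app-based interventions. Higher rates weaken the result, as the 33-44% shows. The Fisher and Pearson calculations also only approximate the planned adjusted mixed model.
- **False positives.** A reader might infer about an even chance or more of at least one spurious stratum result if there is no effect anywhere. That figure is not robust. For 28 stratum tests, with age assumed in three bands, simulation at rates of 5%, 10% and 20% gave 53%, 64% and 67% with Pearson but 20%, 39% and 50% with Fisher. The conclusion does not rest on it.
- **Interaction tests do not cure sparsity.** This stands in full.

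**Conclusion.** The point holds as a correction of method and wording for an exploratory analysis. Separate stratum analyses do not test whether the effect differs, and the analysis section and the Discussion should describe the same approach. If the effect is uniform at 5% versus 20%, with about 42 per arm per city, independent cities and a single contrast, the three cities would disagree at P<.05 in about 72-74% of trials. At an assumed 15% versus 45% the figure is 33-44%. Discordance is therefore likely at the planning rates but not certain. Likewise, empty control cells are a probability (46-63% in the three smallest strata named above, 10-12% per city), not a certainty.

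That city characteristics cannot be separated from city follows from having three cities. That sample source equals city is probable but not established. No primary or secondary conclusion is affected.

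**What to change.** In Evaluation of Intervention Effectiveness, state that subgroup differences will be assessed by one exploratory arm-by-factor interaction test per factor, in the full model on all randomised participants. Stratum estimates with confidence intervals would be shown descriptively and not judged by within-stratum P values. Align the Discussion's moderator statement with this by naming the variables that represent socioeconomic status.

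Use city or CBO once and drop city characteristics as a separate factor. Keep sample source only if it is defined as something other than the CBO. If an SAP already says this, correct the article's wording to match.

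The cost is wording only, and there is time: final follow-up is planned for August 2026 and database lock for December 2026. The downside is that interaction tests will mostly be inconclusive (about 23% power in the example above). Sparse strata will still give very wide or undefined estimates, and the report should say so. Education is also missing for some participants: the Table 1 counts sum to 120 + 121 + 112 = 353 of 381. The education interaction therefore needs a stated handling of those 28.

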## Results

The trial is a 3-arm, parallel-group, randomized controlled trial conducted in collaboration with 3 CBOs located in Mianyang (Sichuan Province), Zibo (Shandong Province), and Hohhot (Inner Mongolia), China. The study protocol was funded in December 2025. Key operational phases, from recruitment to analysis, with specific dates and participant flow, are presented in Figure 1.

**Figure 1. F1:**
[figure not shown]
Participant flowchart (status as of February 2026: baseline assessment and randomization completed; interventions are ongoing). GCEI: group-based conditional economic incentive; HAPA: health action process approach; ITT: intention-to-treat.

### Participant Recruitment

Participant recruitment and screening were conducted from October to December 2025. During this period, 743 eligible MSM from the 3 CBOs were initially identified and assessed. Of these, 362 individuals were excluded for the following reasons: failure to meet predefined inclusion criteria (n=306), declining to participate (n=52), or other logistical reasons (n=4). Consequently, 381 participants provided written informed consent and were formally enrolled in the study. These 381 participants were randomly allocated into 1 of 3 study arms using a computer-generated sequence: HAPA-based cognitive behavioral intervention group (n=128), HAPA plus GCEI intervention group (n=126), and control group (n=127).

### Participant Baseline Characteristics

As shown in Table 1, the baseline sociodemographic characteristics of the participants were well-balanced across the 3 study groups. Specifically, the average ages across the 3 groups were similar, with the HAPA cognitive intervention group averaging 34.5 (SD 9.9) years, the HAPA combined conditional economic incentive intervention group averaging 35.4 (SD 10.6) years, and the control group averaging 34.3 (SD 10.6) years (*F*_2,378_=0.411; *P*=.66). The geographical distribution of participants among the 3 recruitment cities (Mianyang, Zibo, Hohhot) was also balanced and consistent across all groups (*χ*²_4_=0.205; *P*=.96).

**Table 1. T1:** Baseline sociodemographic characteristics of participants (N=381).

Characteristic	Group			*F*/chi-square (*df*)^a^	*P* value
	HAPA^b^ cognitive intervention (n=128)	HAPA+CEI^c^ intervention (n=126)	Control (n=127)		
Age (y), mean (SD)	34.5 (9.9)	35.4 (10.6)	34.3 (10.6)	0.411 (2, 378)	.66
City, n (%)					
Mianyang	42 (32.8)	43 (34.1)	41 (32.3)	0.205 (4)	.96
Zibo	44 (34.4)	41 (32.5)	42 (33.1)		
Hohhot	42 (32.8)	42 (33.3)	44 (34.6)		
Current relationship, n (%)^d^					
Single	51 (39.8)	65 (51.6)	55 (43.3)	3.731 (2)	.16
Has a boyfriend	54 (42.2)	41 (32.5)	52 (40.9)	2.943 (2)	.23
Heterosexual marriage or has a girlfriend	17 (13.3)	12 (9.5)	18 (14.2)	1.424 (2)	.49
Divorced or widowed	13 (10.2)	11 (8.7)	8 (6.3)	1.260 (2)	.53
Education level, n (%)^e^					
Junior high school or below	17 (13.3)	11 (8.7)	9 (7.1)	6.156 (6)	.41
High school or associate degree	50 (39.1)	51 (40.5)	44 (34.6)		
Bachelor’s degree	38 (29.7)	43 (34.1)	48 (37.8)		
Master’s degree or above	15 (11.7)	16 (12.7)	11 (8.7)		
Employment status, n (%)					
Full-time	94 (73.4)	96 (76.2)	98 (77.2)	1.548 (6)	.96
Unemployed or retired	15 (11.7)	15 (11.9)	13 (10.3)		
Part-time	11 (8.6)	7 (5.6)	10 (7.9)		
Student	8 (6.3)	8 (6.3)	6 (4.7)		
Personal monthly income (CNY^f^), n (%)					
≤3000	28 (21.9)	35 (27.8)	23 (18.1)	4.141 (6)	.66
3001‐6000	55 (43.0)	52 (41.3)	61 (48.0)		
6001‐9000	31 (24.2)	28 (22.2)	28 (22.0)		
>9000	14 (10.9)	11 (8.7)	15 (11.8)		
Sexual orientation, n (%)					
Homosexual	101 (78.9)	101 (80.2)	97 (76.4)	2.347 (4)	.67
Bisexual or heterosexual	24 (18.8)	19 (15.1)	23 (18.1)		
Uncertain	3 (2.3)	6 (4.8)	7 (5.5)		

a An *F* test was conducted for Age. All other categories were analyzed with a chi-square test.

b HAPA: health action process approach.

c CEI: conditional economic incentives.

d Multiple selection allowed; percentages do not sum to 100%.

e Due to technical issues with the data collection system, some data on education level are missing.

f 1 CNY=US $0.145.

Furthermore, analyses of various personal and social characteristics revealed no significant group differences. This included educational attainment (*χ*²_6_=6.156, *P*=.41), current relationship status (*P*>.05), employment status (*χ*²_6_=1.548, *P*=.96), level of personal monthly income (*χ*²_6_=4.141, *P*=.66), and sexual orientation distribution (*χ*²_4_=2.347, *P*=.67). In terms of these characteristics, the descriptive profile shows that the majority of participants were either single or in a relationship, were primarily engaged in full-time employment, and reported a personal monthly income concentrated in the range of 3001 to 6000 CNY (US $436.02-$871.76). The predominant self-identified sexual orientation among participants was homosexual.

### Intervention Delivery and Follow-Up Status

Following the baseline assessment, the 3-month active intervention period commenced in January 2026. The intervention delivery, including tailored WeChat messaging, scheduled motivational interviews, and structured in-person group sessions for the HAPA+GCEI arm, is scheduled for completion in April 2026.

### Data Collection and Analysis Timeline

Data collection for the primary outcome and secondary outcomes is scheduled to conclude with the final follow-up assessment in August 2026, with full results expected to be published before December 2026. Database lock and statistical analysis are planned for December 2026.

## Discussion

This protocol outlines a study aimed at enhancing the uptake of HIV PrEP among Chinese MSM through a multifaceted approach, integrating the HAPA and conditional economic incentives. This research addresses the critical public health challenge of low PrEP use among high-risk populations, particularly MSM, who are disproportionately affected by HIV.

The HAPA model, a robust theoretical framework, provides a comprehensive strategy for understanding and promoting health behavior change. By focusing on both motivational and volitional phases, the HAPA model can effectively address the barriers to PrEP initiation and adherence [26]. This approach aligns with international research advocating for theory-driven, stage-matched interventions to bridge the intention-behavior gap, such as motivational interviewing for PrEP uptake among MSM in the United States [37]. However, many existing behavioral interventions in high-income settings do not adequately address the substantial financial barriers that are paramount in contexts like China, where PrEP is not covered by national health insurance [38]. This study directly responds to this gap by integrating HAPA with a pragmatic financial component.

Additionally, the incorporation of economic incentives represents an innovative strategy that leverages the power of financial rewards to encourage health-promoting behaviors. While economic incentives have shown promise in improving antiretroviral therapy adherence [39] and in pilot PrEP studies [33] elsewhere, our GCEI model innovates by applying a group-contingent structure within a Chinese MSM context. Economic incentives can reduce the financial burden associated with accessing PrEP, thereby overcoming one of the significant barriers to its use in the Chinese context [40]. By analyzing objective measures of PrEP initiation and adherence, this study will contribute valuable insights into the effectiveness of integrating behavioral interventions with economic incentives in promoting HIV prevention strategies, which is of global interest [41].

Several practical and operational considerations are crucial to ensuring the trial’s success. To maintain participant engagement and facilitate follow-up, providing clear and accessible information about the study and PrEP is essential. Regular reminders through various communication channels will be used to enhance retention rates. Furthermore, standard training for all staff involved in participant recruitment and data collection will be implemented to ensure high-quality and consistent data throughout the study.

However, this study does have potential limitations. First, the generalizability of the findings may be affected by the implementation through selected CBOs in specific urban Chinese settings, which may limit applicability across different cultural and socioeconomic contexts. The 3-month intervention period may not capture long-term behavioral patterns, suggesting that future studies should incorporate extended follow-up assessments. Additionally, the effectiveness of economic incentives could be influenced by external macroeconomic factors and individual attitudes toward financial rewards, though socioeconomic status will be included as a moderating variable in the analysis.

This study demonstrates several key strengths. An innovative intervention model has been designed by integrating eHealth technologies with established CBO partnerships. The WeChat-based platform is implemented in collaboration with 3 well-established MSM-friendly CBOs (each with 5‐10 y of documented HIV prevention experience), creating a potentially replicable implementation framework. The study design includes comprehensive pilot testing of behavioral change techniques prior to full implementation, with systematic application of HAPA theory across all intervention components. Both individual-level and group-level mechanisms have been carefully operationalized to allow for thorough evaluation. The hybrid intervention approach (combining digital and in-person components) addresses several implementation challenges. Existing social networks will be leveraged through CBO infrastructures, while privacy concerns will be mitigated through discreet eHealth communication channels. The protocol includes specific strategies for cost-effective scaling in resource-limited settings. These design features may provide valuable insights for bridging the intention-behavior gap in PrEP uptake among key populations.

In conclusion, this study outlines a comprehensive research protocol aimed at addressing the pressing challenge of low PrEP uptake among Chinese MSM. By integrating behavioral interventions based on HAPA with conditional economic incentives, we aim to identify effective strategies to enhance PrEP initiation and adherence in this vulnerable population. The outcomes have the potential to inform both public health practice in China and similar global settings by demonstrating how individual-level cognitive support and group-level financial strategies can be synergistically deployed within community-based and digital platforms to enhance HIV prevention.

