**Objective:**

This randomized controlled trial aims to evaluate the effectiveness of HAPA-driven interventions, both alone and combined with GCEI, to enhance PrEP initiation and adherence among high-risk, PrEP-naive MSM in China.

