#### Conditional Economic Incentives

Participants in the combined intervention arm also receive additional peer GCEIs on top of the HAPA intervention. Incentive information is communicated immediately at the start of the intervention. The incentive amounts are determined at the end of the 3-month intervention by the researchers based on the overall completion status of each participant and their peer group according to predetermined conditions.

Participants are formed into peer groups of approximately 6 individuals. These groups participate in structured in-person sessions. Activities are designed to include: introductions and icebreakers, PrEP knowledge quizzes, partner dialogues, “Voicing My Barriers” roundtable discussions, and PrEP scenario role-playing. The objectives are to foster trust, enable deeper peer connection, enhance group belonging, strengthen HIV prevention awareness, identify and overcome barriers to PrEP use, and ultimately increase PrEP initiation rates. Six participants form a peer group, and the economic incentive amount is based on the average completion level of the group. Group-level economic incentives are stepwise reduced based on the group’s average PrEP initiation rate. Participants qualify for US $22 if their group achieves an 80%‐100% rate, US $11 for a 50%‐79% rate, and US $0 for rates below 50%. PrEP initiation is operationally defined as the documented provision of a physician-issued prescription.

The WeChat mini-program automatically records intervention process evaluation indicators, including: (1) whether each participant has read the information messages; (2) the reading time for each message; and (3) each participant’s judgment of whether the information was helpful.

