### Outcomes

The primary outcome indicator of this study is the rate of PrEP initiation, based on formal PrEP prescriptions issued by doctors. The secondary outcome indicators include medication adherence rates after initiating PrEP (based on self-reported adherence and the medication calendar in the mini-program), intention to pay for PrEP (for 3 types of PrEP), PrEP stigma, changes in condom use, and changes in number of sexual partners before and after PrEP use.

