Intervention process and satisfaction evaluation: This evaluates participants’ experience and satisfaction with the mobile health intervention platform (the WeChat mini-program), including usage frequency, overall satisfaction, willingness to recommend it, and specific feedback on its ease of use, interface design, information resources, medication reminders, recording functions, and data privacy protection.Risk compensation behavior assessment: It investigates changes in participants’ sexual behavior patterns during the intervention to assess the possibility of risk compensation, including changes in the frequency of same-sex intercourse, number of male sexual partners, and condom use frequency compared to baseline.PrEP uptake status: Based on the current PrEP status at follow-up, it further explores specific reasons for noninitiation or discontinuation, sources of medication acquisition, methods of recording medication use, episodes of treatment interruption, occurrence of adverse drug reactions, partner awareness, psychological experiences related to PrEP use, and willingness to recommend it.Dynamic measurement of PrEP-related cognition: It reapplies key items from the validated HAPA-based PrEP cognition scale to assess changes in postintervention cognition, including self-efficacy for PrEP initiation and maintenance, positive and negative outcome expectations, perceived HIV risk, and action planning.Reassessment of PrEP decision and payment willingness: It re-evaluates participants’ perception of pricing and willingness to use different PrEP regimens at market prices, as well as their views on potential models for cost-sharing.Follow-up on PrEP perceived stigma and MSM group cohesion: It uses a brief mental health scale to assess emotional states over the past week, remeasures PrEP perceived stigma levels, and evaluates changes in perceived cohesion within the MSM community.

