The sexually transmitted infections testing data (HIV, syphilis, hepatitis B, and hepatitis C) from participants at baseline and during 2 follow-up visits are collected. All tests are performed using standardized diagnostic kits (Wondfo Biotech) according to the manufacturer’s protocols. Serological results are recorded as binary outcomes (positive or negative). For participants who initiated PrEP during the study, adverse drug reaction evaluations are integrated throughout the PrEP medical service process. A formal safety stopping rule is prespecified. The trial will be halted immediately if the independent Data and Safety Monitoring Board identifies clear, serious, and related adverse events attributable to the study procedures that pose unacceptable risks to participants, or if new, definitive external evidence emerges that renders the trial unethical or obsolete.

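### The Discussion calls adherence objectively measured, but as the Outcomes section defines it, only initiation rests on an external record

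*Protocol article*

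**What the plan says.** The Abstract's objective names adherence next to initiation: the interventions are meant "to enhance PrEP initiation and adherence among high-risk, PrEP-naive MSM in China". The aim at the end of the Introduction does the same.

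The Outcomes section defines the two differently. The primary outcome is "the rate of PrEP initiation, based on formal PrEP prescriptions issued by doctors". Adherence after initiation is a secondary outcome, "based on self-reported adherence and the medication calendar in the mini-program".

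The Discussion then gives both the same property: "By analyzing objective measures of PrEP initiation and adherence, this study will contribute valuable insights". The limitations paragraph later in the Discussion covers generalisability, the length of the intervention and outside influences on incentives. It does not mention how adherence is measured.

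**The concern.** Objective measurement tells a reader that a result does not depend on what the participant chooses to say. A prescription meets that description; self-report does not. With one adjective covering both outcomes, a reader of the results could take an arm difference in reported adherence as a difference in drug-taking.

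This matters more here because the recording tool and the intervention share a channel. Under Tailored Health Messages, the active arms are sent personalised messages through the WeChat mini-program, some of them about keeping to the regimen. The medication calendar sits in the same mini-program. Under Control, the comparison arm receives nonpersonalised prevention information. Encouragement to adhere could therefore change how diligently or how favourably a man reports, apart from any change in what he takes. What is at stake is the interpretation of a secondary outcome that the article also names as an objective.

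**Working it through.** The plan states no figure on this point, so the check is mainly a comparison of text.

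**1. Is there an objective source for adherence anywhere in the article?**

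- *Outcomes*: two sources are named, self-report and the calendar. This is a stated definition, not a gap left for a fuller document.
- *Conditional Economic Incentives*: "The WeChat mini-program automatically records intervention process evaluation indicators, including: (1) whether each participant has read the information messages", followed by reading time and the participant's view of helpfulness. Doses are not on that list of automatic records.
- *Measurements and Follow-Ups*, biological tests: "The sexually transmitted infections testing data (HIV, syphilis, hepatitis B, and hepatitis C) from participants". No drug level is listed.
- *Ethical Considerations*: participants buy the drug themselves at market price. No study dispensing record or pill count is described.

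None of these supplies an objective adherence measure.

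**2. Who fills in the calendar?** The article does not say outright. The follow-up questionnaire asks participants about "methods of recording medication use, episodes of treatment interruption", and the satisfaction items treat recording as a platform function that users rate. Together with the absence of doses from the automatic records, this points to participant entry. That is an inference. The contradiction does not need it, because self-report alone already fails the description.

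**3. Does blinding help?** The Methods say that outcome assessors and analysts are blinded. For a self-reported outcome the data come from the participant, so blinding those who handle the data afterwards does not remove reporting differences.

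**4. How large could a distortion be?** Suppose true adherence is *a* in every arm, adherent men report correctly, and a share *r* of non-adherent men report adherence. Then

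recorded adherence = *a* + (1 − *a*) × *r*

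and the spurious difference between arms is (1 − *a*) × (*r* active − *r* control).

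The Introduction gives adherence among MSM in China as 29.9% to 41.1%, so (1 − *a*) runs from 1 − 0.411 = 0.589 to 1 − 0.299 = 0.701. Each percentage point by which over-reporting differs between arms would thus add about 0.6 to 0.7 points to the recorded difference. If over-reporting is equal, the difference is 0. The documents give no value for *r* in any arm, so no figure for the distortion itself can be stated.

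**The case against.** The strongest reply is that this is one adjective in a Discussion sentence. The Outcomes section states the adherence sources openly, adherence is secondary, the stated objectives do not claim objective measurement, and self-report is a reasonable choice in a trial that supplies no drug. All of that is correct. Using self-report is not the error; describing it as objective is.

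A second reply is that differential reporting is conjecture. The mini-program serves the whole trial for assessment and assignment, controls also receive push notifications, and the reminder and recording functions are not said to be confined to the active arms. This stands too. A reader might infer that adherence results will be biased towards the active arms, but the documents support only that they could be. Nor do they say that controls are sent nothing beyond testing and condom messages: the Control section gives those as examples of what is included.

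A third reply is that the adherence comparison will be too imprecise for a modest distortion to be distinguished from chance. At the planning rates of 5% and 20%, initiators would number about 127 × 0.05 = 6.35 among controls, and 126 × 0.20 = 25.2 or 128 × 0.20 = 25.6 in the active arms. One control would then be worth roughly 16 percentage points (1/6.35 = 0.157). This is a fair reason not to attach a size to the bias. It is also a further reason for caution about the adherence result, and it does not make the measure objective.

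**Conclusion.** The inconsistency holds on the face of the article. The word objective fits initiation and does not fit adherence as the article defines it, and no limitation warns the reader. The primary outcome and the sample size are untouched.

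Two limits apply. That the calendar is participant-entered is a well-supported inference, not a stated fact. That reporting differs by arm is a possibility created by the shared channel; its size is unknown, and under the simple model above it is zero if over-reporting is equal. A reader might go further and conclude that the adherence objective cannot be addressed at all. The article does not support that: self-report and a calendar can still be compared between arms, provided the result is described as what was reported and recorded.

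The correction is worth making because it changes what the trial may conclude about a named objective. There is time for it: the final follow-up is scheduled for August 2026, and database lock and analysis for December 2026.

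**What to change.** 1. In the Discussion, limit the word objective to initiation.
2. In the outcomes and the results, label adherence as self-reported and app-recorded. Self-reported alone would drop the calendar, which the Outcomes section names as a source.
3. Add to the limitations that an arm difference in this outcome is not by itself evidence of a difference in drug-taking.
4. Among initiators, report by arm the share with any calendar entry, and show the self-report and calendar results separately. This makes unequal recording visible, though it cannot make the measure objective.

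A refill or repeat-purchase check is not proposed. The follow-up items listed cover where medication was obtained and whether treatment was interrupted, but not refills, and the answers would themselves be self-reported.

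The cost is wording, one or two descriptive rows from data already planned, and a weaker adherence claim.
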